### **Adverse Reactions**

An adverse reaction is an AE that is caused by the vaccine.

### **Suspected Adverse Reaction (SAR)**

An adverse event for which there is a reasonable possibility that the drug caused the adverse event. ‘Reasonable possibility’ means that there is evidence to suggest a causal relationship between the drug and the adverse event. A suspected adverse reaction implies a lesser degree of certainty about causality than adverse reaction which implies a high degree of certainty.

### **Serious Adverse Events**

A Serious Adverse Event (SAE) is defined as an AE that results in any of the following outcomes:

- death
- life threatening (i.e., an immediate threat to life)
- inpatient hospitalization or prolongation of an existing hospitalization
- a persistent or significant incapacity or substantial disruption of the ability to conduct normal life functions
- congenital anomaly/birth defect
- other medically important event\*

\* Medical and scientific judgment will be exercised in deciding whether expedited reporting is appropriate in other situations, such as important medical events that may not be immediately life threatening or result in death or result in hospitalization but may jeopardize the patient or may require intervention to prevent one of the other outcomes listed above. These will also usually be considered serious.

### **Unexpected Adverse Events**

An AE is considered unexpected if it is not listed in the Investigator Brochure or Package Insert (for marketed products) or is not listed at the specificity or severity that has been observed. “Expected” does not mean that the event is expected with pharmacologically similar drugs, the underlying disease(s) or concomitant medications.

### **Suspected and Unexpected Serious Adverse Reaction (SUSAR)**

A SUSAR is a Suspected Adverse Reaction that is both Serious and Unexpected. Under 21 CFR 312.32, SUSARs will be reported by the IND Sponsor to the FDA and to all participating investigators in an IND Safety Report.

### **New Onset of Chronic Illness (NOCI)**

The new onset of chronic illness is defined as a diagnosis of a new medical condition that is chronic in nature, including those potentially controllable by medication (e.g., diabetes, asthma). Any NOCI will be recorded in the same manner as unsolicited AEs.

## Unanticipated Problems

An Unanticipated Problem (UP) is any incident, experience, or outcome that is

1. unexpected in terms of nature, severity, or frequency in relation to
  - a. the research risks that are described in the IRB-approved research protocol and informed consent document; Investigator's Brochure or other study documents; and
  - b. the characteristics of the subject population being studied; and
2. related or possibly related to participation in the research; and
3. places subjects or others at a greater risk of harm (including physical, psychological, economic, or social harm) than was previously known or recognized. (An AE with a serious outcome will be considered increased risk.)

## Unanticipated problem that is not an Adverse Event (UPnonAE)

An UP that does not fit the definition of an AE, but which may, in the opinion of the investigator, involve risk to the subject, affect others in the research study, or significantly impact the integrity of research data; for example, occurrences of breaches of confidentiality, accidental destruction of study records, or unaccounted-for study drug.

## Protocol Violation

Any change, divergence, or departure from the study procedures in an IRB-approved research protocol that has a major impact on the subject's rights, safety, or well-being and/or the completeness, accuracy or reliability of the study data.

## Protocol Deviation

Any change, divergence, or departure from the IRB approved study procedures in a research protocol that **does not** have a major impact on the subject's rights, safety or well-being, or the completeness, accuracy and reliability of the study data.

## 9.2 Preexisting Conditions, Conditions, Worsening of Pre-existing Condition

Stable chronic conditions which are present prior to enrollment and do not worsen are not considered AEs and will be accounted for in the subject's medical history. Exacerbation or worsening of pre-existing conditions are defined as AEs and are evaluated using the same criteria described in **Section 9.3.2** in this protocol.

## 9.3 Assessment of Adverse Events

Assessment of safety will include clinical observation and monitoring of hematological, chemical, and immunologic parameters. Subjects will be closely monitored for 30 minutes following each immunization. Additionally, subjects will return to the clinic on Days 3, 7, 14, and 28 following each vaccination for clinical assessments, and periodically thereafter until completion. All AEs will be recorded through Day 28 after each vaccination. Injection site reactions will be assessed until day 14 or until resolved. After that period only SAEs, UPs, and NOCIs ([Section 9.1](#)) will be recorded.

All AEs will be graded for severity and assessed for relationship to the study product. Reactions

will be graded as described in this protocol. A study clinician will be available 24 hours a day during the study period. Should a subject call a study clinician to report an AE, it will be fully documented in the subject's study chart, and discussed with the PI.

All local and systemic reactions will be captured on the appropriate source documents and CRIMSON Data System. Those assessed as serious will be further reported on the Sponsor's SAE/UP report form. AEs judged to be possibly, probably, or definitely related to the study product will be followed to adequate resolution. All concomitant medications will be collected through day 28 after each vaccination; new chronic medications will be collected for the remainder of the study.

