### **Study Day 28 $\pm$ 3 Days**

1. Perform directed history and assessment of any physical complaint.
2. Record vital signs.
3. Obtain urine for dipstick testing.
4. Review pregnancy prevention counseling.

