2. A reaction of similar nature having previously been observed with this type of vaccine and/or formulation
3. The event having been reported in the literature for similar types of vaccines
4. Whether or not there is another identifiable cause

All local (injection-site) reactions will be considered causally related to vaccination.

Reports will further classify AEs as follows: Related (all AEs that are assessed as definitely, probably, or possibly related) and Unrelated (all AEs assessed as unlikely or definitely not related), as per [Table 4](#) below. When reporting to regulatory authorities and IRBs is needed, AE relationship will be determined per [Table 4](#).

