#### **12.5.2 Immunization**

Possible local vaccine reactions include pain, swelling, erythema, induration, limitation of limb movement for several days, lymphadenopathy, or pruritus at the injection site. Local subcutaneous (SQ) nodules, believed to be granulomatous reactions to aluminum, have been observed with use of aluminum-based adjuvants. Thus, most aluminum-absorbed vaccines are injected intramuscularly (IM) rather than SQ. Systemic reactions such as fever, chills, headache, fatigue, malaise, myalgia, and joint pain may also possibly occur, with some reactions moderate or severe.

As with any vaccine, immediate hypersensitivity reactions including urticaria, anaphylaxis, or other IgE-mediated responses are possible. There is a theoretical possibility of risks about which we have no present knowledge. Subjects will be informed of any such risks should further data become available.

Subjects may be asked to defer routine immunization (such as influenza) until 14 days following

vaccination. This may increase the risk that the subject will be infected with an influenza virus during this period.

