## Appendix C: Toxicity Table

These tables are modified versions of the FDA Toxicity Grading Scale for healthy adult and adolescent subjects enrolled in Preventive Vaccine Clinical Trials to be used to grade adverse events.

Tables for Clinical Abnormalities

| Local Reaction to Injectable Product | Mild (Grade 1)                                  | Moderate (Grade 2)                                                                | Severe (Grade 3)                                             | Potentially Life Threatening (Grade 4)       |
|--------------------------------------|-------------------------------------------------|-----------------------------------------------------------------------------------|--------------------------------------------------------------|----------------------------------------------|
| Pain                                 | Does not interfere with activity                | Repeated use of non-narcotic pain reliever > 24 hours or interferes with activity | Any use of narcotic pain reliever or prevents daily activity | Emergency room (ER) visit or hospitalization |
| Erythema/Redness *                   | 2.5 – 5 cm                                      | 5.1 – 10 cm                                                                       | > 10 cm                                                      | Necrosis or exfoliative dermatitis           |
| Induration/Swelling **               | 2.5 – 5 cm and does not interfere with activity | 5.1 – 10 cm or interferes with activity                                           | > 10 cm or prevents daily activity                           | Necrosis                                     |

\* In addition to grading the measured local reaction at the greatest single diameter, the measurement should be recorded as a continuous variable.

\*\* Induration/Swelling should be evaluated and graded using the functional scale as well as the actual measurement.

| Vital Signs * /Systemic adverse events | Mild (Grade 1)               | Moderate(Grade 2)            | Severe (Grade 3)         | Potentially Life Threatening (Grade 4)                 |
|----------------------------------------|------------------------------|------------------------------|--------------------------|--------------------------------------------------------|

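### Section 9.3 leaves the recording window for new injection-site reactions unclear, and the visit lists omit a site examination at the 14-day post-booster visit and at every 28-day visit

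*Protocol*

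**What the plan says.** Local AEs are part of the primary endpoint (Section 3.2.1). Section 9.3 governs their collection in three consecutive sentences:

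- The first sets a general window for events of every kind: "All AEs will be recorded through Day 28 after each vaccination".
- The second sets a separate rule for the site of vaccination: "Injection site reactions will be assessed until day 14 or until resolved".
- The third restricts what is kept once an unnamed window has closed: "After that period only SAEs, UPs, and NOCIs".

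Two further rules apply. Section 9.3 adds that "AEs judged to be possibly, probably, or definitely related to the study product will be followed to adequate resolution", and Section 9.3.3 that "All local (injection-site) reactions will be considered causally related to vaccination".

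The visit lists in Section 6.4 name the injection site as part of the physical examination at 3 and 7 days after every dose, and at 14 days after doses 1, 2 and 3 (Days 14, 70, 134). The Day 28 list reads "Perform directed history and assessment of any physical complaint". Days 84, 148 and 328 carry almost the same line, and so does Day 314, which is 14 days after the booster.

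Section 12.5.2 warns of a local reaction linked to the adjuvant: "nodules, believed to be granulomatous reactions to aluminum, have been observed with use of aluminum-based adjuvants". Section 1.3 gives a similar warning. Neither gives a frequency or a time of onset.

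**The concern.** Two things do not fit together. First, the recording rule for a site reaction first noticed between Day 15 and Day 28 depends on how one reads the third sentence, so two people entering data could treat the same event differently. Second, examination ends before the recording window does, and after the booster it ends before even the shorter window.

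At stake is whether local AEs are ascertained completely, and equally across doses, in a first-in-human study whose primary endpoint includes them. A subcutaneous nodule is the natural example. The protocol warns of it, but Table 3 does not solicit it by name, and a subject may not raise it unprompted. Section 11.2(d) also compares the number of AEs in the two weeks after the first vaccination with the number after later ones, and that comparison assumes the same search after each dose.

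**Working it through.** No stated figure is under challenge, so the check is a comparison of the text.

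**Step 1: the window.** Take a non-serious site reaction first noticed on Day 20 that is neither an unanticipated problem nor a new chronic illness.

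| Rule applied | Recorded? |
|---|---|
| First sentence (all AEs to Day 28) | Yes |
| Third sentence, if the period ends at Day 28 | Yes |
| Third sentence, if the period ends at Day 14 | No |

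The second sentence has its own ambiguity, because it does not say whether the earlier or the later of its two end points applies. For a reaction lasting to Day 25, the earlier reading ends assessment at Day 14 and the later reading at Day 25. The rule that related AEs are followed to resolution, together with the rule that all local reactions count as related, favours the later reading. Those rules concern a reaction already found. They do not say how a new one is to be found.

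**Step 2: the visit lists (Section 6.4).**

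| Dose | Site examination listed | Not listed at 14 days | Not listed at 28 days |
|---|---|---|---|
| 1 | Days 3, 7, 14 | – | Day 28 |
| 2 | Days 59, 63, 70 | – | Day 84 |
| 3 (Group 2) | Days 123, 127, 134 | – | Day 148 |
| Booster | Days 303, 307 | Day 314 | Day 328 |

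**Step 3: last listed examination to the 28-day visit.**

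- Doses 1 to 3: 28 − 14 = 14 days.
- Booster: 328 − 307 = 21 days, of which 314 − 307 = 7 fall inside the Day 14 window of Section 9.3.

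These intervals locate the gap. They do not measure missed events, because examinations take place on single days in any case.

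**Step 4: the comparison in Section 11.2(d).** Within two weeks of vaccination there are 3 listed site examinations after each of doses 1, 2 and 3, and 2 after the booster. If this has any effect, it is towards fewer local AEs being found after the booster.

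**Step 5: size.** An expected under-count would need the rate of reactions starting after the last examination and the share that subjects do not report. The protocol gives neither, so no figure is offered.

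**The case against.** The best defence is that the rules already cover most of this. The sentence on all AEs has no exception for local events, so a nodule reported at the Day 28 visit is recordable. An abnormal sign is an AE under Section 9.1, and an event not listed in Appendix C can be graded under Section 9.3.2, where Grade 1 has no size limit. Each 28-day visit includes a history, and Appendix B marks an interim clinical evaluation there. The visits for later doses include a focused physical examination, and a clinician can be reached at all hours. Section 12.5.2 links the nodule risk to the preference for intramuscular injection, which is the route used here. Examining sites actively for a shorter time than AEs are recorded is a legitimate design choice.

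Most of this stands, and it rules out several stronger readings that a reader might infer:

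- That site assessment simply stops at Day 14. The sentence goes on to allow assessment until resolution.
- That local AEs are excluded from the Day 28 window. The text makes no such exception.
- That nodules are in fact under-counted, or that missed cases would fall mainly on the 47 µg group because it receives the most adjuvant. The protocol gives no rate, onset time or dose relation for nodules.
- That a nodule below the lowest size in the induration row ("2.5 – 5 cm and does not interfere with activity") goes unrecorded. Grading and recording are separate, and Section 6.6 has any site reaction measured during the diary period without a minimum size.

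The defence leaves three things unanswered. The period in the third sentence is undefined. A reaction that starts after the last listed examination and is not mentioned has no planned route to detection, since the symptom card runs for only 6 days after each dose. And Day 314 is not a design choice of this kind, because it departs from the protocol's own Day 14 window and from the matching visits after doses 1 to 3.

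**Conclusion.** The point holds in a limited form. Section 9.3 does not fix one window for new injection-site reactions, and five visit lists (Days 28, 84, 148, 314 and 328) omit a site examination that the windows would call for. The firmest item is Day 314, an internal inconsistency that makes local-AE ascertainment unequal between the booster and earlier doses in the Section 11.2(d) comparison. The 28-day omissions are a weakness and not an error. They matter only for a reaction that begins after the last listed examination and that the subject does not report.

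The conclusion rests on the visit lists being followed as written. Staff who examine the site anyway would close the gap in practice. The size of any under-count is unknown from the document, and no conclusion about safety at any dose follows from it. The change is worth making because it is cheap and local AEs are in the primary endpoint.

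**What to change.** In Section 9.3:

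- State that new injection-site reactions are recorded through Day 28 after each vaccination, as for all other AEs, and that unresolved ones are followed to resolution.
- Replace the reference to the period with an explicit day.

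In Section 6.4:

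- Add the injection-site examination to Day 314, so that it agrees with Section 9.3 and with Days 14, 70 and 134.
- Add an injection-site check to Days 28, 84, 148 and 328.
- Record the diameter of any nodule found, whatever its size.

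All five visits already take place. The cost is a few lines of text, about a minute per visit, and a few more mild local AEs in the tables. If some visits have already been held under the current lists, the report should say at which visits the site was examined, so that the Section 11.2(d) comparison can be read accordingly.

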## **1.3 Previous Human Experience**

This Phase 1 study is the first time that this conjugated vaccine will be given to humans. The components of the vaccine (unconjugated antigen and adjuvants) have been evaluated in prior clinical trials described below. Details on adverse events (AEs) and immunogenicity results of these trials are described in the Investigator's Brochure.

Pfs25 formulated with the water-in-oil emulsion Montanide ISA51 was evaluated in a dose escalating Phase 1 trial in malaria naïve adults, together with the *Plasmodium vivax* homologous antigen Pvs25 [Wu et al 2008]. Vaccinations were halted due to local and systemic reactogenicity, including 2 cases of erythema nodosum in subjects who received 1 dose of 20 µg Pvs25/ISA51, and 2 leukemoid reactions (one in the Pfs25 5 µg group which occurred 14 days after second vaccination, and one in the Pvs25 20 µg group which occurred 120 days after first vaccination). Ten subjects received 1 dose of 5 µg Pfs25/ISA51; 2 subjects were withdrawn due to severe local reactions and 3 others were withdrawn for unrelated reasons.

Of the 5 subjects who received a second dose of vaccine, all had detectable antibody responses, with 1 subject's responses peaking at 7322 ELISA units. Serum from this subject resulted in >90% reduction of oocyst counts in a transmission blocking assay; serum from 3 of the other 4 responders was also tested and showed moderate transmission blocking activity (18-47% reduction in oocysts), with transmission blocking activity correlating with anti-Pfs25 antibody levels.

Clinical development was halted due to the unfavorable safety profile of the Montanide ISA51 formulation. While some degree of local reactogenicity was expected with this water-in-oil formulation, the systemic events which occurred were not predicted by animal toxicity studies or previous human experience with these antigens or with this adjuvant.

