#### **9.5 Halting Rules**

The PI will closely monitor study data as they become available and will make determinations regarding the presence and grading of AEs. The AEs will be evaluated with regard to the known complications associated with administration of vaccine components. If a dose of vaccine is considered unacceptably reactogenic (as described in the following criteria), the study will be halted. No new enrollments and no further vaccinations will be administered by the Investigators until reviewed by the SMC and study IND Sponsor. A report of SMC recommendations will be submitted to the IRBs. The following criteria will be used to define unacceptable reactogenicity of the malaria vaccine (AEs that are possibly, probably, or definitely related to the vaccine will be considered "Related" as per [Table 4](#) and will be summarized as such):

1. One or more subjects experience an SAE as defined in [Section 9.1](#) of this protocol that is determined to be possibly, probably, or definitely related to the vaccine, **or**
2. One or more subjects experience a hypersensitivity reaction that is probably or definitely related to the vaccine, **or**
3. Any severe clinical illness occurs that is not explained by a diagnosis that is unrelated to vaccination, **or**
4. Two or more subjects in any dose cohort experience any Grade 2 or higher laboratory abnormality (see [Appendix C](#)), or Grade 3 systemic AE that is determined to be possibly, probably, or definitely related to the vaccine as defined in this protocol, **or**
5. One or more subjects experience erythema nodosum.
6. Two or more volunteers in a single dose cohort experience Grade 3 or higher injection site induration or any abscess formation.

The IRBs, the NIAID, the FDA, or other government agencies may discontinue the study at any time. Subsequent review of serious, unexpected, and related AEs by the SMC or IRB, the IND sponsor, the FDA, and other regulatory authorities may also result in suspension of further administration of vaccine at the clinical site. The FDA, other regulatory authorities, and the study sponsor(s) retain the authority to suspend additional enrollment and administration of vaccine for the entire study as applicable.

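### The halting rules have no time limit, but from Day 28 after a dose an event that counts toward one need not be recorded unless it is an SAE, an unanticipated problem or a new chronic illness

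*Protocol*

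**What the plan says.** **Recording.** Section 9.3 sets the general window: "All AEs will be recorded through Day 28 after each vaccination". Injection-site reactions are followed to Day 14 or resolution. Then: "After that period only SAEs, UPs, and NOCIs" are recorded. Another sentence of the same section says, without any day limit, that local and systemic reactions are all to be captured on source documents and in the data system.

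**Halting.** Section 9.5 lists six criteria, none with a time window. Rule 5 reads "One or more subjects experience erythema nodosum" and asks for neither seriousness nor a causal link. Rule 4 needs at least two subjects in the same dose cohort with a laboratory abnormality of Grade 2 or above, "or Grade 3 systemic AE that is determined to be possibly, probably, or definitely related to the vaccine". The decision starts from the investigator's review: "The PI will closely monitor study data as they become available".

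**Unanticipated problems.** Section 9.1 requires three things together. The event must be "unexpected in terms of nature, severity, or frequency in relation to" the described risks and the study population, "related or possibly related to participation in the research", and such that it raises the known risk of harm.

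**The concern.** Safety is the primary objective, and whether further doses are given depends on the halting rules. Those rules apply at any time, while the requirement to record their inputs largely lapses 28 days after each dose. An event can therefore satisfy a rule, or be the second case that Rule 4 needs, without any instruction to enter it as an AE.

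Rule 4 is the most exposed, because counting to two within a cohort relies on complete records. Two other uses of AE data are affected. Section 9.4.4 sends a summary of AEs to the safety committee before its review, and section 6.10 ends a subject's vaccinations after certain related Grade 3 AEs, also without a time limit. In section 11.2, the proportion with at least one AE could miss such events. The signed-rank comparison there uses only the two weeks after each dose and is unaffected.

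**Working it through.** The protocol attaches no figure to this point. The nearest are the detection probabilities in section 11.4, and they reproduce to rounding: 1 − (1 − 0.275)^5 = 0.7997 and 1 − (1 − 0.052)^30 = 0.7985, against 0.80 stated. They concern serious *or severe* AEs and presuppose that such an event is recorded once it occurs. After Day 28 that is assured only for the serious ones.

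**Step 1: which halting events fall outside recording?** Take a non-serious event between Day 28 and the next dose.

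| Event | Halting rule | Unanticipated problem? | New chronic illness? |
|---|---|---|---|
| Erythema nodosum, judged unrelated | Rule 5, one case | No: fails the relatedness condition | No, if acute |
| Related Grade 3 systemic AE, e.g. myalgia | Rule 4, two in a cohort | Need not be: section 12.5.2 already describes severe systemic reactions | No |
| Related Grade 2 white-cell count at Day 270 | Rule 4, two in a cohort | Only if also judged unexpected and risk-increasing | No |

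The third row concerns data the protocol itself collects. Section 6.4 schedules a blood count for Group 2 at Day 270, which is 270 − 120 = 150 days after dose 3 and 300 − 270 = 30 days before the booster. Table 3 lists the white-cell count as a solicited laboratory AE. Blood drawn just before dosing on Days 56, 120 and 300 raises the same question, since the protocol does not say whether such a sample belongs to the old interval or to the new window.

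**Step 2: how long is the uncovered time?** Dose days are 0, 56, 120 and 300 for Group 2, and 0, 56 and 300 for Group 1 with booster. Days 0 to 28 after each dose count as covered, and each dosing day counts as Day 0 of the new window.

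Uncovered days = next dose day − (previous dose day + 28) − 1

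- Dose 1 to 2: 56 − 28 − 1 = 27
- Group 2, dose 2 to 3: 120 − 84 − 1 = 35
- Group 2, dose 3 to 4: 300 − 148 − 1 = 151
- Group 2 total: 27 + 35 + 151 = 213; 213/300 = 71%
- Group 1, dose 2 to booster: 300 − 84 − 1 = 215
- Group 1 total: 27 + 215 = 242; 242/300 = 81%

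**Step 3: visit windows.** Section 6.4 allows dose 2 on Days 56–70, dose 3 on Days 92–148 and the booster on Days 286–314. The gaps then range over:

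- 27–41 days, dose 1 to 2
- 0–63 days, dose 2 to 3
- 109–193 days, dose 3 to 4
- 187–229 days, Group 1 dose 2 to booster

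Only the dose 2 to 3 gap can vanish, when dose 2 is late and dose 3 early.

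**The case against.** The strongest reply is that most events that matter would still be caught. Unanticipated problems need not be serious, and the SAE definition includes other medically important events. Erythema nodosum is not among the risks in section 12.5, so a case judged related would plausibly be an unanticipated problem. An AE that a subject telephones in is documented in the chart and discussed with the investigator, whatever the day. Group 2 has visits with a history at Days 175 and 270, and every dosing visit has a history, a focused examination and safety bloods. Section 6.9 lets the investigator defer a dose for any threatening condition.

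Much of this stands, and it makes the gap narrower. It does not close it. The unanticipated-problem route fails for the cases in the table. Telephone reports depend on the subject calling, and a chart note is not an AE record. For Group 2, no visit is scheduled between Days 28 and 56 or between Days 84 and 120. The contraindications in section 6.8 do not ask about erythema nodosum or a past Grade 3 systemic AE. The sentence that captures all reactions does not rescue the text either: it conflicts with the Day 28 limit.

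A reader might also cite the earlier trial's leukemoid reaction, "which occurred 120 days after first vaccination", as proof that this plan would miss such an event. The documents do not support that. It followed a different antigen and adjuvant (Pvs25/ISA51), section 1.3 ascribes the unexpected systemic events most likely to that combination, and a similar event judged related would plausibly be recorded as an unanticipated problem or as medically important. It shows only that late events are conceivable.

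**Conclusion.** The point holds in a limited form: sections 9.3 and 9.5 do not match, and a definable class of halting-rule events has no recording requirement over 71% (Group 2) or 81% (Group 1 with booster) of the 300 days before the last dose, on the nominal schedule. These shares measure calendar time, not the chance of a vaccine-related event, which may well be concentrated soon after dosing.

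Three stronger readings should be avoided:

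- That no non-serious AE is recorded after Day 28. Unanticipated problems and new chronic illnesses can be non-serious and are recorded.
- That a single late Grade 3 systemic AE meets Rule 4. It needs two subjects in a cohort.
- That the time after Day 328 enlarges the problem. It follows the last dose, and because Table 2 staggers enrolment by only weeks, there is essentially no dose left to halt.

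Assumptions: the period named in section 9.3 is read as ending at Day 28, although the sentence directly follows the Day 14 rule for injection sites. The relatedness condition in Rule 4 is read as covering laboratory values too; if it does not, the gap is wider. The Investigator's Brochure and consent form are not at hand, so whether erythema nodosum would count as unexpected cannot be settled.

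**What to change.** Reconcile section 9.3 with section 9.5 so that the AE-recording window and the halting rules cover the same events and the same period, and bring the sentence on capturing all reactions into line with the result. How to resolve it is for the sponsor; nothing here judges the halting criteria themselves.

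One route on the data-collection side is to state that an event named in a halting rule is recorded whenever it is found at a visit or blood draw already scheduled, leaving the Day 28 limit for all other AEs. The same sentence could say how a pre-dose laboratory value is assigned.

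The cost is about one sentence, with no added visits or tests. The downside is a few late, mostly unrelated events to record and assess.
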